**Other measures**		

Physical activity levels	Physical Activity Scale for the Elderly (PASE) Pedometer worn for 7 days	0, 13, 36 weeks
Treatment credibility	Treatment Credibility Scale	1,12 weeks
Participant success of blinding	Questionnaire	13, 36 weeks
Healthcare consumption and related costs	Questionnaire; health system records	0, 5, 9, 13, 36 weeks
Adverse events	Participant log-book	Throughout
Adherence - treatment session attendance; home exercise or gel application	Participant log-book; Therapist treatment records; Questionnaire	Throughout

#### Secondary outcome measures

A number of secondary measures will be included (Table 3). The Hip Osteoarthritis Outcome Scale (HOOS) is a patient-administered measure that assesses the patient's opinion of their hip and associated problems over the previous week. It consists of five subscales; pain, other symptoms, function in daily living, function in sport and recreation, and hip-related quality of life. A normalised score (100 indicating no symptoms and 0 indicating extreme symptoms) is calculated for each subscale [24].

A number of functional performance tests and musculoskeletal impairments will be measured at baseline and at 13 weeks. The passive range of hip flexion, extension, abduction, internal rotation and external rotation will be measured using clinical methods and an inclinometer. The test retest reliability ICCs for these measures ranged from 0.82 to 0.94 in 25 patients with hip OA tested one week apart [25]. For all measures, two trials will be performed and the mean reading used in analysis. Hip flexion, extension and abduction will be measured in supine while internal and external rotation will be measured in sitting

An instrumented manual muscle tester will be used to measure maximum, normalised isometric strength (peak torque; Nm/kg) of the hip abductor, extensor, flexor and internal and external rotator muscles. Our reliability ICCs ranged from 0.65 to 0.85 in six patients with hip OA tested a week apart [25]. Measurements of hip abductors and extensors will be taken in supine while those of the flexor and rotator muscles will be taken in sitting. Maximum voluntary isometric torque of the quadriceps and hamstring muscles at 60° knee flexion will be measured in sitting using a KinCom isokinetic dynamometer (reliability ICCs were 0.85 for quadriceps and 0.85 for hamstrings for ten patients with painful hip OA). Testing will comprise two maximal contractions with the peak value used for analysis.

Several functional tests will be included. The stair climb test [26] involves timing how long it takes participants to ascend and descend six steps at their own pace. For the 30 second sit-to-stand test, the number of times participants can rise to a full standing position from sitting and return to sitting in 30 seconds is counted [27]. Walking performance will be assessed by calculating walking velocity (m/sec) as participants walk 20 meters with the instructions 'walk as quickly as you can without overexerting yourself' [28]. Dynamic standing balance will be assessed by the step test [29] and the 4-square step test [30].

In a subset of participants, gait analysis will be performed at baseline and at 13 weeks. Kinematic and ground reaction force data will be recorded simultaneously for five walking trials in usual footwear at self-selected pace using a 3-D motion analysis system with12 cameras (Vicon MX, Oxford, UK) and three force plates (AMTI, Massachusetts, USA) concealed in the floor. Kinematics will be derived from the standard Davis-Kadaba marker set using Vicon Plug-in Gait model. Data will be combined using inverse dynamics to yield measures of external joint moments. The main measures will be peak external hip adduction and abduction moments, peak external hip flexion and extension moments, pelvic drop/rise in the frontal plane and pelvic rotation ranges of motion, and peak and total range of hip motion in the sagittal and transverse planes. Reliability in our laboratory is good for the measures we have subjected to reliability testing, with ICCs of 0.56 to 0.95 (the majority > 0.80) from six patients with hip OA and six controls tested twice one week apart.

The Assessment of Quality of Life instrument version 2 (AQoL II) has 20 questions that cover six dimensions of health-related quality of life including independent living, social relationships, physical senses, coping, pain and psychological wellbeing. The AQoL has strong psychometric properties and is more responsive than other widely-used scales [31,32]. It produces a single utility index that ranges from -0.04 (worst possible health-related quality of life) to 1.00 (full health-related quality of life). A clinically important difference in health-related quality of life can be defined as a change of 0.04 AQoL units [33]. The AQoL will be collected at weeks 0, 13, and 36.

Habitual physical activity will be measured in two ways, using a questionnaire and using a pedometer. The Physical Activity Scale for the Elderly (PASE) will be used to measure both the level and type of recreational and occupational physical activity undertaken by participants over the previous week. The PASE was developed and validated in samples of older adults (age 55+ years) [34]. A pedometer (HJ-005 Omron Healthcare, Japan) will be worn for a week on three occasions (baseline, 13 weeks and 36 weeks) to record the number of steps taken per day. Participants will be asked to wear the pedometer full time during their waking hours. Pedometers have been found to be a simple and inexpensive means to estimate physical activity levels [35,36]. It is recommended that at least three days of sampling are needed to accurately assess activity levels given differences between weekends and weekdays [37].

The Arthritis Self Efficacy Scale will be used to measure psychological status. It has three subscales that assess self-efficacy for control of pain management, physical function and other arthritis symptoms. Prior studies have supported both the reliability and validity of this scale [38]. Pain catastrophizing will be measured using the 13-item Pain Catastrophizing Scale. It measures tendencies to ruminate about pain, magnify pain, and feel helpless about pain. It has high internal consistency (coefficient alpha = .87) and is associated with heightened pain, psychological distress, and physical disability [39]. We will use the Coping Attempts Scale of the Coping Strategies Questionnaire to assess the use of pain coping skills [40]. This 42-item scale measures how often a patient engages in 7 different pain coping strategies. This instrument has demonstrated sensitivity to change from treatment in chronic pain samples as well as good internal consistency and construct validity [41].

Participants will rate their perceived overall change and their change specifically in pain and in physical function with treatment (compared to baseline) on seven-point ordinal scales (1-much worse to 7-much better). Scales of this kind are frequently used as an external criterion for comparison with changes in scores of other outcomes [42]. Measuring patient perceived change using a rating of change scale has been shown to be a clinically relevant and stable concept for interpreting truly meaningful improvements from the individual perspective [43]. We will also dichotomise the group according to their perceived change rating where *improved *will be defined as 'moderately' or 'much' better, and *not improved *will be defined as 'slightly' better and below. The proportion of improved participants from each group will determine success of the treatment.

#### Other measures

A number of other measures will be obtained (Table 3). Participant adherence will be obtained by recording the number of physiotherapy sessions attended (out of a maximum number of ten). Those in the active physiotherapy group will complete a daily log-book to record the number of home exercise sessions completed during the treatment phase. To indicate adherence to the home program during the six-month follow-up period, participants in both groups will be mailed a short questionnaire at Weeks 24 and 36 which asks how many times in the past week they have performed the home exercises or applied the gel. Adverse events and the use of co-intervention will be recorded in a log-book and by open-probe questioning by the assessor at trial completion. At the 13 week and 36 week measurement time points, study participants will be asked to indicate which treatment they believe they have received (active or sham) and reasons for that choice to assess the success of blinding.

Information on health care costs and direct non-health care costs over the last month will be collected retrospectively at week 0, 5, 9, 13, and 36 by questionnaire. Direct health care costs will include costs of physiotherapy attendance (assumed zero in the sham group), additional health provider visits (doctors, specialists, other health care professionals), investigative procedures, purchase of prescription and over the counter medication, and hospitalisation. These will be valued using published prices for medical costs. Direct non-health care resources will include number of lost days from work.

The monetary valuation of health status pre- and post-treatment is potentially a more comprehensive patient relevant measure of treatment gains than measures of either a clinical outcome or health-related quality of life. A simple open-ended questionnaire will ask participants in each group about their willingness to pay for the treatment given the outcomes they experience.

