### Economic evaluation

The economic evaluation will be conducted from the perspective of the Australian health care system and the individual patient. The primary economic evaluation will take the form of a cost effectiveness study of the cost per extra quality adjusted life years (QALYs). QALYs will be calculated using the AQoL scores over 36 weeks. Differences in mean change from baseline for the AQoL to each time point will be weighted by the time from baseline using generalised linear regression modelling adjusting for baseline levels of the AQoL to construct QALYs, and then compared between groups. Differences in the mean cost between groups will be calculated using generalised linear regression modelling. Incremental cost per QALY will be calculated as the ratio of the difference in mean cost to the difference in mean QALYs with 95% confidence intervals calculated using Fieller's theorem. As supplementary analyses the incremental cost per extra person with a clinically significant improvement in function, and per extra person perceived to be recovered will be calculated

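### One-month cost recall leaves about weeks 13 to 32 without patient-reported costs, while the QALYs in the cost-effectiveness ratio span 36 weeks

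*Protocol article*

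**What the plan says.** On costs, the Other measures section states that health care and direct non-health care "costs over the last month will be collected retrospectively at week 0, 5, 9, 13, and 36", by questionnaire. The items named include provider visits, investigations, prescription and over-the-counter medication, hospitalisation and days lost from work. Table 3 gives the same five time points but a wider source: "Questionnaire; health system records". The text does not mention the records, and Table 3 does not say what period they cover.

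On effects, the Secondary outcome measures section states: "The AQoL will be collected at weeks 0, 13, and 36". The Economic evaluation section states: "QALYs will be calculated using the AQoL scores over 36 weeks".

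On combining the two, that section states: "Differences in the mean cost between groups will be calculated using generalised linear regression modelling", and then: "Incremental cost per QALY will be calculated as the ratio of the difference in mean cost to the difference in mean QALYs". It gives no cost horizon and no rule for the time between recall windows.

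A contact point already exists inside the follow-up period. For adherence to the home programme, "participants in both groups will be mailed a short questionnaire at Weeks 24 and 36".

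**The concern.** During treatment the cost questionnaires are four weeks apart, so a one-month recall is almost continuous. After week 13 the interval to the next questionnaire is 23 weeks, but the recall stays at one month, so most of follow-up is never asked about.

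This bears on H4, the cost-effectiveness hypothesis. The numerator and denominator of a cost-per-QALY ratio should refer to the same period. The main cost of the active programme, up to ten sessions in 12 weeks, falls outside the gap and can be counted from attendance. Later differences in visits, medication, imaging or admissions fall mostly inside it. If the recalled months are simply summed and physiotherapy lowers later use, the sum overstates its net cost. If physiotherapy raises later use, the sum understates it.

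The evaluation takes the individual patient's perspective as well as the health system's, so items that only the patient can report count towards the result.

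**Working it through.** The article states no number of weeks costed, so there is no figure of its own to reproduce. The check is interval arithmetic on the stated schedule.

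**Inputs.** Post-baseline cost questionnaires at t = 5, 9, 13 and 36 weeks, each recalling one month (Other measures; Table 3 for the times). QALY horizon 36 weeks (Economic evaluation). Follow-up from week 13 to week 36, so 36 − 13 = 23 weeks. The month is not defined in weeks, so its length m is taken as 4 weeks, 30.4/7 = 4.35 weeks, or 31/7 = 4.43 weeks.

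**Formula.** Each questionnaire covers the interval from t − m to t. Coverage is the union of these intervals within weeks 0 to 36.

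**With m = 4.** The windows are 1–5, 5–9, 9–13 and 32–36. Coverage is 12 + 4 = 16 weeks, and 16/36 = 44%. The follow-up gap is 32 − 13 = 19 weeks.

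| Month length (weeks) | Weeks covered | Share of 36 | Follow-up gap (weeks) | Gap as share of 36 | Gap as share of 23 |
|---|---|---|---|---|---|
| 4 | 16.0 | 44% | 13 to 32 (19.0) | 53% | 83% |
| 4.35 | 16.7 | 46% | 13 to 31.65 (18.65) | 52% | 81% |
| 4.43 | 16.9 | 47% | 13 to 31.57 (18.57) | 52% | 81% |

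A further 0.6 to 1 week just after baseline is also uncovered.

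**If the week-36 month were scaled to all of follow-up.** With m = 4, the factor is k = 23/4 = 5.75. This multiplies the estimate and its standard error alike, so it does not measure the precision lost. The relevant comparison is with observing all 23 weeks. Let monthly cost have the same mean and variance σ² throughout, with correlation ρ between months:

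- variance of the scaled month: k²σ²
- variance of the full period: σ²[k + k(k − 1)ρ]
- ratio of standard errors: √{k / [1 + (k − 1)ρ]}

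The ratio is 1 at ρ = 1 (perfectly stable costs) and √5.75 = 2.4 at ρ = 0 (independent months). The article does not give ρ, so only this range can be stated. The comparison also assumes that the week-36 month is typical of the whole of follow-up. If it is not, scaling adds bias as well.

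**The case against.** A reader might infer that weeks 13 to 32 are wholly unobserved. The document does not support that. Table 3 lists health system records, which could plausibly hold visits, investigations and admissions. The Procedure section says that medication and co-interventions are recorded, and Other measures adds a log-book and open questioning by the assessor at trial completion. These are real routes to some of the information. But no period is stated for the records, the text on cost collection omits them, and the log-book and questioning are not described as costing sources. Over-the-counter medication and lost work days are unlikely to be in health system records. The objection narrows the gap without closing it.

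A reader might also infer that the ratio sets a 16-week cost against a 36-week effect. That would follow only if the recalled months are simply summed, and the Economic evaluation section does not say so.

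It can fairly be said that a condensed article may leave the cost horizon and any bridging rule to a fuller document. That stands for the analysis rule, so its absence alone is not the point here. It does not stand for the recall length and time points, which the article fixes. No later analysis plan can recover what no participant was asked, and multiple imputation could fill such a window only by extrapolation.

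Finally, the request to refrain from other treatments and the exclusion of people planning back or lower limb surgery within 9 months may reduce later costs. They do not make them zero or equal between groups. Short recall is also a legitimate choice for accuracy, but here it is bought with most of the follow-up period.

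**Conclusion.** The point holds in a limited form and should be addressed. As written, the cost questionnaires cover about 44% to 47% of the 36 weeks over which QALYs are built, and leave 18.6 to 19 weeks of follow-up without patient-reported costs. This rests on reading the recall period literally as one month, and on the questionnaire being the main source for items that records are unlikely to hold.

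How much of the gap the health system records fill cannot be judged from the article. The effect on the incremental cost or on the ratio cannot be put in figures either, because no cost data are given. What can be said is conditional: summing the recalled months truncates the incremental cost, and scaling up the week-36 month rests 23 weeks of cost on one month.

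The consequence is confined to H4 and the economic evaluation. The primary outcomes, pain and physical function at 13 weeks, are unaffected.

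**What to change.** 1. Add the cost items to the questionnaire already mailed at week 24, with recall since week 13 (11 weeks).
2. Reword the week-36 recall to run since week 24 (12 weeks). With the existing windows this covers 12 + 11 + 12 = 35 of 36 weeks for a 4-week month. Wording the week-5 recall as since baseline would close the remaining week.
3. State that costs are accumulated over the same 36 weeks as the QALYs.
4. Reconcile the Other measures text with Table 3 on cost sources, and state which items and what period the health system records cover.
5. Adjust the cost regression for the week-0 cost already collected. This does not fill the gap, but it uses data in hand to improve the comparison.

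The cost is a few items on an existing mailing, reworded recall periods and an ethics notification. The downside is that recall over 11 to 12 weeks is less exact than over one month, particularly for small and frequent items such as over-the-counter medication.

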### Sample size

Our two primary endpoints are hip pain measured on a VAS and WOMAC physical function score. The minimum clinically important difference to be detected in OA trials is a change in pain of 18 mm (on 100 mm VAS) [44] and a change of six physical function WOMAC units (out of 68) [45]. Based on our previous data, we assume a common between-subject standard deviation of change of 30 mm for pain VAS and 12 units for WOMAC physical function as well as a baseline to 13 weeks correlation in scores of 0.6. These statistics indicate a smaller standardised effect size of interest (Cohen's *d*) of 0.5 for the WOMAC measure than the *d *of 0.6 for pain. The required sample for an analysis of covariance of change in scores controlling for the baseline value of the variable when *d *is 0.5, power is 0.9 and type I error is set at .05 is 54 participants per group. In addition, at 54 participants per group the power will be even greater for pain. Allowing for an approximate 15% drop-out rate, we will recruit 64 participants per group.

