### Data and statistical analysis

The primary analysis of the data will be undertaken using the principle of intention-to-treat (ITT). Our ITT analysis will include all participants including those who have missing data and those who are not fully compliant with the protocol. Some attrition is anticipated despite the fact that we will implement procedures to minimise loss to follow-up and participant withdrawal, and maximise adherence. Multiple imputation methodology will be employed to account for missing data [46].

Demographic and clinical characteristics as well as baseline data will be presented to assess the baseline comparability of the intervention groups. These variables will also be examined for those participants who withdraw from the study and those who remain.

Descriptive statistics will be presented for each group as the mean change (standard deviation, 95% confidence intervals) in the outcomes from baseline to each time point. Differences in mean change from baseline to each time point will be compared between groups using generalised linear regression modelling adjusting for baseline levels of the outcome measure. Model assumptions will be checked by standard diagnostic plots.

Improvement between active and sham physiotherapy groups based on the perceived ratings of change will be compared using log binomial regression and presented as relative risks with 95% confidence intervals.

As part of the secondary analyses of the primary outcomes at 13 and 36 weeks, we plan to conduct a separate analysis to estimate the effect of treatment in the hypothetical scenario of full adherence to randomised treatment modality. Adherence will be defined as attendance at more than 80% of scheduled treatment sessions and 60% of prescribed home exercise sessions in the active physiotherapy group. This is based on definitions used in another study of manual therapy and exercise in hip OA [47]. Analytical methods for this will utilise instrumental variables methodology involving two stage least squares estimation [48].

An index (with bootstrap 95% confidence intervals) to assess the success of participant blinding will be computed [49].

No statistical adjustment will be made for multiple testing. All tests will be two sided and carried out at the 5% level of significance. Any changes to the study design or analysis plan will be documented with full justification.

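### The SDs in the sample-size section are labelled as SDs of change, but 54 per group comes from a reduction that applies to SDs of the scores; the section must state which SD was used

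*Protocol article*

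**What the plan says.** The Sample size section sets the differences to detect as "a change in pain of 18 mm (on 100 mm VAS") and "a change of six physical function WOMAC units (out of 68"). For variability it says "we assume a common between-subject standard deviation of change of 30 mm for pain VAS and 12 units for WOMAC physical function", citing the group's previous data, and adds "a baseline to 13 weeks correlation in scores of 0.6". Dividing gives standardised effects of 18/30 = 0.6 for pain and 6/12 = 0.5 for function, so function is the limiting outcome.

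The sizing method is introduced as "The required sample for an analysis of covariance of change in scores controlling for the baseline value of the variable", and the result is stated as "power is 0.9 and type I error is set at .05 is 54 participants per group". Allowing for about 15% drop-out brings this to 64 per group, 128 in all.

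The Data and statistical analysis section matches that method: change from baseline is compared between groups with adjustment for the baseline value. It also says "All tests will be two sided and carried out at the 5% level of significance".

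The protocol gives no SD for the scores at baseline or at 13 weeks.

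**The concern.** Adjusting for baseline leaves a fraction 1 − r² of the variance of the 13-week score. The variance of a change score has already been reduced by the same correlation, so baseline adjustment removes a different, usually smaller, share of it. Multiplying an SD of change by the score-based factor counts the correlation twice.

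The limiting primary outcome is affected. If the label is right and the SDs are similar at the two visits, the chance of missing a true 6-unit difference in function is about 17–18% instead of the stated 10%. A reader who relied on 90% power would then take a null function result as stronger evidence than it is.

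**Working it through.** **Inputs.** From Sample size: difference 6 units (function) and 18 mm (pain); SD 12 and 30, labelled as SDs of change; r = 0.6; power 0.90; 54 per group. From Data and statistical analysis: two-sided 5%. So (1.95996 + 1.28155)² = 10.507. Powers use the normal approximation unless marked.

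**1. Reproduce the plan's figure.**
- Without covariate: n = 2 × 10.507 × 144 / 36 = 84.06 per group.
- Multiplied by 1 − 0.6² = 0.64: 53.8, rounded up to 54. (The t distribution gives 55.)
- Drop-out: 54 / 0.85 = 63.5, rounded up to 64. This step is correct.

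The plan's residual variance for function is therefore 0.64 × 144 = 92.2, which treats 12 as the SD of the 13-week score.

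**2. The factor that belongs to an SD of change.** Let s be the 13-week SD and q the ratio of baseline SD to 13-week SD.
- Var(change) = s²(1 + q² − 2rq)
- ANCOVA residual variance = s²(1 − r²), whether the outcome is change or the final score
- Residual variance as a fraction of Var(change): f = (1 − r²) / (1 + q² − 2rq)

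With equal SDs (q = 1), f = 0.64 / 0.80 = 0.80. With q = 1.2, 1 + 1.44 − 1.44 = 1, so f = 0.64. That is the ratio at which the plan's factor would suit an SD of change.

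**3. Function, with 12 as an SD of change and equal SDs (assumption).**
- Residual variance: 0.80 × 144 = 115.2
- Standard error at 54 per group: √(2 × 115.2 / 54) = 2.066
- Power: 6 / 2.066 = 2.905; Φ(2.905 − 1.960) = 82.8% (t: 82.1%)
- Difference detectable with 90% power: 3.2415 × 2.066 = 6.7 units
- n for 6 units with 90% power: 2 × 10.507 × 115.2 / 36 = 67.2, rounded up to 68 per group; 68 / 0.85 = 80 recruited per group
- If all 64 per group were retained: power about 88.5%

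**4. Function, over a range of SD ratios (12 as an SD of change).**

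| Baseline SD / 13-week SD | f | Power at 54 per group |
|---|---|---|
| 0.8 | 0.94 | 76% |
| 0.9 | 0.88 | 79% |
| 1.0 | 0.80 | 83% |
| 1.1 | 0.72 | 87% |
| 1.2 | 0.64 | 90% |
| 1.25 | 0.60 | 92% |

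**5. Pain, with 30 as an SD of change.** Equal SDs would imply a baseline SD of 30 / √0.80 = 33.5 mm. The Participants section requires a VAS of at least 40 on a 100 mm scale. A variable confined to 40–100 cannot have an SD above 30 (half its range), and a uniform spread over it has an SD of 60 / √12 = 17.3. Equal SDs are therefore not a usable assumption for pain. For a given baseline SD b (assumed), the 13-week SD is 0.6b + √(900 − 0.64b²).
- b = 15: 13-week SD 36.5; residual variance 0.64 × 36.5² ≈ 852; standard error 5.62; power 89%.
- b = 25: 13-week SD 37.4; residual variance ≈ 893; standard error 5.75; power 88%.

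On the plan's own 0.64 factor, pain power would be about 97%.

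**6. Could a different test explain 54?** A one-sided 5% test with f = 0.80 gives 55 per group, which is close. The protocol specifies two-sided tests, so this is not the explanation.

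**The case against.** The strongest reply is that only a label is wrong. If the previous data gave 12 and 30 as SDs of the scores, then 54 per group, 90% power and 128 participants are all correct, and the error is two surplus words. The pain inputs lean this way: 30 mm as an SD of change needs a 13-week SD of about 36–37 mm when the baseline SD is 15–25 mm, whereas 30 mm as a 13-week score SD needs no such strain. This is suggestive only. The baseline reading may differ somewhat from the screening reading, and the deciding data are not shown.

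A second reply is that the stated inputs do not determine power under the SD-of-change reading, because no visit-specific SDs are given. That is correct. A reader might infer from the label that the plan's own inputs give 82–83% power for function and that the trial is therefore underpowered. The documents do not support this: the figure needs equal SDs at both visits, and a baseline SD 1.2 or more times the 13-week SD would restore 90%. Nor do they support carrying the equal-SD assumption over to pain, which would give 93–94%, because of the entry floor.

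Neither reply removes the mismatch. The section names one kind of SD, calculates with the factor for another, and states nothing that would reconcile them.

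**Conclusion.** The point holds as an inconsistency in the Sample size section. A label of SD of change and a result of 54 per group with 90% power cannot both stand unless the baseline SD is about 1.2 times the 13-week SD, which is not stated. The documents do not show which of the two is the slip.

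The consequence depends on the answer:
- **SDs of scores:** no effect on sample size or power.
- **SDs of change:** function power at 54 per group is about 82–83% if SDs are equal at both visits, and about 76–92% for baseline/13-week ratios of 0.8 to 1.25. Pain power is about 88–89% for an assumed baseline SD of 15–25 mm.

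All of these take r = 0.6 and 54 analysable participants per group as given. The mismatch is certain; a loss of power is possible but not established.

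**What to change.** Check the previous data and state in the Sample size section which SD the 12 units and 30 mm are.

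- **If they are SDs of the scores:** remove the words that make them SDs of change, and keep 54 per group and 90% power.
- **If they are SDs of change:** keep 128 participants and restate function power from the baseline and 13-week SDs in those data, naming the assumption. With equal SDs the statement would be about 82–83% power for 6 units, or 90% for about 6.7 units. Recompute pain power in the same way, with a baseline SD compatible with the entry requirement of VAS at least 40, and do not quote 93%.

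The cost is one or two sentences and a look at existing data. No participants are added, and no endpoint or analysis changes. The only downside is that, in the second case, the stated power may be less favourable. Recruitment has begun, so the correction should be recorded with its reason, in line with the protocol's own commitment to document changes to the design or analysis plan.
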